### Sample size

#### Numbers required (power analysis)

There is limited empirical evidence on the effectiveness of current transition programs in regard to engagement with and retention in adult services or on rates of deterioration in illness control on which to base power calculations. In the diabetes literature, approximately 70% of adolescents will make some form of transition from paediatric to adult services [23, 24]. Using a predicted attrition rate of 30%, a sample size of 70 participants will be needed to obtain the minimum sample of 49 adolescents required for this study. A sample of 49 adolescents will have greater than or equal to 80% power at 5% one-sided alpha, to detect an increase in the rate of successful transition from paediatric to adult care from 70%.

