### Trial design

The trial is designed to be a two centre, pragmatic, single arm, mixed methods cohort study. As this is a single arm study, there will be no randomisation or allocation process on recruitment. Results will be compared with existing historical data from our previous research as well as others.

Source of historical data from the following source:Perry L, Steinbeck KS, Dunbabin JS, Lowe JM. Lost in transition? Access to and uptake of adult health services and outcomes for young people with type 1 diabetes in regional New South Wales. Med J Aust 2010 Oct;193(8):444–9.Audit of 239 young adults aged 18–28 years with type 1 diabetes accessing five adult diabetes services before 30 June 2008 in three geographical regions of New South Wales [23]Garvey KC, Markowitz JT, Laffe LMB. Transition to Adult Care for Youth with Type 1 Diabetes. Curr Diab Rep 2012 Oct;12(5):533–541 [24].Data were collected between August 2004 and October 2005 through face-to-face interviews with over 200 clinicians in 68 clinical services in tertiary paediatric hospitals in New South Wales, providing information on approximately 4200 patients

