### Explanation for the choice of comparators

Based on the number of patients which fits the eligibility criteria within the hospital network each year, and the anticipated recruitment based on previous adolescent studies of 1:4 approached actually consenting, it was unlikely that adequate power would be achieved if we were to recruit for a comparator group within the resourced time frame available. The necessary updates and debugging in mobile technology and their cost, coupled with the uncertainty of success based on previous literature guided the choice of a single arm study. It was important that we had more knowledge about the TMApp’s utility and durability of use before progressing to a comparator study.

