#### Engagement and retention with adult service

Successful engagement with the adult service at 6 months will be defined as confirmed attendance at least one appointment with the adult service by six months post discharge from paediatric care (i.e. after the last paediatric appointment). This will be considered as a *successful transfer* to adult services. This number is chosen because most chronic conditions have guidelines on the optimal number of specialist visits per year with a frequency varying from 3 to 6 months. Routine annual visits are less likely and will be recorded as such.

*Engagement* with the adult service will be assessed, with consent of the young person/parent, (provided at enrolment) via phone call to the young person and nominated adult service at 6 months post discharge from paediatric care. If the young person has not attended the service they were referred to, they will be asked if they are attending an alternate service and for consent to contact this service. Young people who cannot be contacted at 6 and 12 months post discharge from the paediatric service will be considered to have unsuccessful engagement and be a *failed transfer* to adult care.

*Retention* within the adult service will be defined as at least one confirmed attendance with the adult service in the preceding 6 months at 12 and 18 months follow up. These data will be collected, with consent, via phone call to the young person and the adult service to obtain information regarding attendance at the adult service at 12 and 18 months follow up. Young people who cannot be followed up at 12 and 18 months post discharge from the paediatric service will be considered to not be retained by the adult service (*failed retention*).

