## Statistical methods

### Statistical methods for primary and secondary outcomes

The primary outcome as the percentage of adolescents who successfully engage and secondary outcomes of the percentage who are retained within the adult health care services will be described using a 90% exact binomial confidence interval. If the lower confidence limit is less than or equal to 70%, the TMApp would not be considered effective in terms of increasing rates of engagement and retention within the adult services.

Participant demographics, clinical characteristics and study outcomes will be described using standard methods, including frequencies and percentages for categorical variables, and mean, standard deviation, median, quartiles and range for continuous variables. Kaplan-Meier methods will be used for time-to-event variables. Study outcomes will be described in the total cohort as well as by chronic illness group, acknowledging that sub-group numbers will limit further analyses.

Linear, logistic or proportional hazards regression models will be used to examine predictors of study outcomes including TMApp use, age, gender, illness, transition readiness and mental health status in univariate models and models adjusted for potential confounders including other transition programs, use of other applications and deterioration in illness control. All effects will be presented with confidence intervals where possible.

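### The 70% line for judging TMApp is a diabetes figure for an undefined transition, so neither crossing nor missing it can be attributed to the app

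*Protocol article*

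**What the plan says.** The sample size section of the protocol article gives the reference rate: "In the diabetes literature, approximately 70% of adolescents will make some form of transition from paediatric to adult services". It then states: "A sample of 49 adolescents will have greater than or equal to 80% power at 5% one-sided alpha", the aim being "to detect an increase in the rate of successful transition from paediatric to adult care from 70" per cent. No target rate follows. The same section opens by admitting that evidence for power calculations is limited.

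The decision rule is in the statistical methods for primary and secondary outcomes: "If the lower confidence limit is less than or equal to 70%, the TMApp would not be considered effective". It applies to engagement and retention alike. The primary objective is also worded as effectiveness of the app on engagement rates.

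The endpoint is defined under Engagement and retention with adult service as "confirmed attendance at least one appointment with the adult service by six months post discharge from paediatric care". Retention requires a further attendance in the six months before the 12- and 18-month follow-ups. The inclusion criteria admit any chronic physical illness and require agreement to use the app and be followed for 18 months. The section on the choice of comparators gives "anticipated recruitment based on previous adolescent studies of 1:4 approached actually consenting". Other transition support may continue alongside the app.

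The Trial design section describes one historical source as "Audit of 239 young adults aged 18–28 years with type 1 diabetes accessing five adult diabetes services" before mid-2008. It also describes clinician interviews from 2004 to 2005.

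**The concern.** A single-arm study that tests against a fixed rate answers one question: is this cohort's rate above that number? It speaks to the app only if the number is what the same young people would have achieved without the app, under the same definition and scoring.

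Here the two differ in several stated ways. The benchmark is for diabetes, while the cohort has any chronic physical illness. The benchmark refers to an unspecified form of transition, while the endpoint is confirmed attendance by six months. The same 70% is reused for retention at 12 and 18 months, which the quoted figure does not describe. About one in four of those approached are expected to consent, and participants may be using transition services that themselves affect attendance.

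If the rule is applied as it stands, any difference in volunteer selection, illness mix, era or loss to follow-up would be read as the presence or absence of an app effect.

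**Working it through.** **Inputs.** From the sample size section: reference rate 70%, one-sided 5%, at least 80% power, 49 evaluable, 30% attrition, 70 enrolled. From the statistical methods: 90% exact binomial interval, whose lower limit is a one-sided 5% limit. From the engagement section and the missing-data section: participants who cannot be contacted, and data that stay missing, count as not engaged. Assumed here, because the documents give no values: no-app rates of 75, 80 and 85%, and loss fractions of 10, 20 and 30%.

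**The plan's own figures.** 49 / (1 − 0.30) = 70. The target rate is not stated. An exact one-sample test of 70% with n = 49 has 80.9% power at a true rate of 85%, so 85% is the inferred target. The arithmetic is sound.

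**The rule as a count.** Find the smallest x whose lower 90% exact limit exceeds 70%.
- n = 49: x = 40 (81.6%), lower limit 70.1%; at x = 39 the limit is 67.8%.
- n = 70: x = 56 (80.0%), lower limit 70.5%; at x = 55 the limit is 68.9%.

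**Probability of clearing 70% when the app does nothing, no losses.** This is P(Bin(49, p) ≥ 40) or P(Bin(70, p) ≥ 56), with p the rate without the app.

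| No-app rate p | n = 49 | n = 70 |
|---|---|---|
| 70% | 4.8% | 4.1% |
| 75% | 18.3% | 20.6% |
| 80% | 47.2% | 57.1% |
| 85% | 80.9% | 90.6% |

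The n = 49 column fits the protocol only if the lost participants are dropped from the denominator, which the missing-data rule does not do.

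**Same calculation at n = 70 with losses scored as failures.** With a fraction L lost independently of engagement, the scored rate is p(1 − L). For example, 0.80 × 0.90 = 0.72, and P(Bin(70, 0.72) ≥ 56) = 8.4%.

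| No-app rate p | L = 10% | L = 20% | L = 30% |
|---|---|---|---|
| 75% | 1.5% | 0.03% | below 0.01% |
| 80% | 8.4% | 0.3% | below 0.01% |
| 85% | 29.8% | 1.8% | 0.02% |

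**The other direction.** Suppose the app works and true engagement is 90%. At 20% loss the scored rate is 0.90 × 0.80 = 0.72 and the limit clears 70% with probability 8.4%. At 30% loss the scored rate is 0.63 and the probability is 0.2%. If exactly 49 of 70 are followed and all 49 engage, the lower limit for 49/70 is 59.7%, which still does not clear 70%.

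**The case against.** The strongest reply has four parts.

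First, the rule states only the negative side: a limit at or below 70% means not effective. A reader might infer that the protocol commits to declaring the app effective above 70%, and that a useless app would be so declared up to 91% of the time. The text contains no such declaration. The primary objective and the aim of detecting an increase make the positive reading natural, but it remains an inference. The 91% also belongs to the extreme case of no losses and an 85% no-app rate.

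Second, a reader might infer that the benchmark is simply too lenient. The documents do not support a fixed direction. Volunteer selection and concurrent services may raise the rate, while scoring losses as failures lowers it. Attendance confirmed by the adult service or hospital databases may recover some lost participants, so effective loss may be below the predicted 30%.

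Third, the cited sources are not available here. That they give no 6-month transfer rate among those leaving paediatric care is read from short descriptions in the article and cannot be asserted of the papers themselves. Nor do the documents say how many participants use other transition services; they say only that these are permitted and recorded.

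Fourth, the authors chose a historical comparison openly, justified it by feasibility and deferred a comparator study. They already plan to describe outcomes by illness group. That is fair, and the single-arm design is not challenged here. But these acknowledgements are not carried into the decision rule. The planned regression on app use does not supply a no-app rate, and the app analytics are cohort-level only.

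**Conclusion.** The point stands as one about interpretation. The 70% line is not described as the no-app rate for this cohort, endpoint or time window, and it is not described as a retention rate at all. The nominal 5% error holds only if the no-app rate, as scored, is 70%.

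Over the assumed ranges at n = 70, the chance that an inert app clears the line runs from practically zero to 91%, depending on the unknown no-app rate and on how many lost participants count as failures. At 20 to 30% loss even a substantial benefit would usually be missed. Neither outcome can therefore be credited to, or held against, the app. These figures rest on the assumed no-app rates, on loss independent of engagement, and on the protocol's scoring of missing as not engaged.

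A narrower conclusion also fits the protocol's own account: it seeks knowledge of utility before a comparator study and, under Interim analyses, calls the study primarily observational.

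**What to change.** Reword the decision sentence in the statistical methods. Report the engagement and retention rates with their 90% exact intervals. Report a lower limit above 70% as this consenting cohort exceeding a historical diabetes figure, and a limit at or below 70% as not exceeding it. In neither case describe TMApp as effective or ineffective.

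Where the clinic data mentioned in the Discussion allow, show the same hospitals' pre-study rate under the same 6-month definition beside the result.

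The diabetes participants may be shown descriptively, as the planned illness-group summaries already provide. They should not be called a like-for-like comparison with 70%, because the endpoint, time window and selection still differ.

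The cost is a narrower conclusion. No extra participants are needed, and the clinic-data comparison is optional.

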### Methods in analysis to handle protocol non-adherence and any statistical methods to handle missing data

Handling of non-adherence is not called for other than recording non-adherence data as an outcome.

Missing data will be managed as recording only. If data are missing and remain missing from any time point of collection the assumption will be that this represents non-engagement with the adult service.

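### The sample size removes 30% of participants as attrition, while the analysis counts the unreached as not engaged, so the stated power does not belong to the stated analysis

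*Protocol article*

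**What the plan says.** Four parts of the protocol article bear on this point.

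- **Numbers required (power analysis).** The benchmark comes from the diabetes literature, where "approximately 70% of adolescents will make some form of transition from paediatric to adult services". Attrition is a deduction: "Using a predicted attrition rate of 30%, a sample size of 70 participants will be needed to obtain the minimum sample of 49 adolescents". The claim is that "A sample of 49 adolescents will have greater than or equal to 80% power at 5% one-sided alpha", and the aim is "to detect an increase in the rate of successful transition from paediatric to adult care from 70" per cent. No target rate is given, and no time point is given for the 30%.
- **Statistical methods for primary and secondary outcomes.** The engagement percentage is to be "described using a 90% exact binomial confidence interval". The decision rule is: "If the lower confidence limit is less than or equal to 70%, the TMApp would not be considered effective".
- **Engagement and retention with adult service.** "Young people who cannot be contacted at 6 and 12 months post discharge from the paediatric service will be considered to have unsuccessful engagement". Such participants are classed as a failed transfer.
- **Methods for non-adherence and missing data.** "If data are missing and remain missing from any time point of collection the assumption will be that this represents non-engagement".

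The Primary outcome section also allows engagement at 6 months to be established from the adult service or from self-report, with hospital databases as a supplement.

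**The concern.** The same participants are treated in two incompatible ways. In the sample-size calculation, those lost leave the denominator and 49 remain. In the analysis they stay in the denominator as failures, so 70 are analysed.

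In a single-arm study with one threshold, this matters directly. Each participant of unknown status lowers the observed engagement rate, and the rule compares that rate with a fixed 70%. The power figure ignores this. A verdict of not effective could then reflect loss to follow-up rather than anything the app did or failed to do.

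**Working it through.** **Inputs from the article:** benchmark 70%; one-sided 5% level, that is, the lower limit of the exact 90% interval; 70 enrolled; 30% attrition, leaving 49; claimed power at least 80%.

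**Assumption:** the article gives no alternative rate. I use 85% and show 80% to 90% where it matters.

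**Formulas.** The exact lower limit for x engaged out of n is the 5% quantile of a Beta(x, n − x + 1) distribution. Success requires x ≥ c, where c is the smallest count whose lower limit exceeds 70%. Power at true rate p is P(Bin(n, p) ≥ c).

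**1. Reproducing the plan's figure**
- 49 / (1 − 0.30) = 70, as stated.
- For n = 49, 39/49 gives a lower limit of 67.8% and 40/49 gives 70.1%, so c = 40. The exact one-sided error at 70% is 0.048.
- Power is 0.472 at 80%, 0.809 at 85% and 0.979 at 90%. It reaches 80% at about 84.8%.
- The normal approximation for 70% against 85% agrees: [(1.645√0.21 + 0.842√0.1275) / 0.15]² ≈ 49.4.

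The arithmetic is therefore sound for 49 participants with full data and a true rate of about 85% or higher.

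**2. The rule as the analysis would apply it**
- With unreached participants counted as failures, n = 70. Here 55/70 gives a lower limit of 68.9% and 56/70 gives 70.5%, so c = 56. The exact one-sided error at 70% is 0.041.
- Power is 80% when about 83.0% of all enrolled are confirmed engaged, and 0.906 when 85% are.
- At most 70 − 56 = 14 participants (20%) can be unascertained if the rule is to be attainable.
- With 21 unascertained and all 49 others engaged, the result is 49/70 = 70.0%, 90% CI 59.7% to 78.9%. This fails, and it does not depend on the assumed 85%.

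**3. Smaller losses.** Assume 85% engagement among those ascertained and a fixed number m unascertained. Power is P(Bin(70 − m, 0.85) ≥ 56).

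| Unascertained at 6 months | Ascertained | Power |
|---|---|---|
| 0 | 70 | 0.91 |
| 4 (about 5%) | 66 | 0.60 |
| 7 (10%) | 63 | 0.25 |
| 14 (20%) | 56 | 0.0001 |
| 21 (30%) | 49 | 0 |

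If loss is instead random for each participant, power is P(Bin(70, 0.85 × (1 − loss)) ≥ 56): 0.63 at 5% loss, 0.30 at 10%, 0.02 at 20% and 0.0002 at 30%. The last value is not zero because the number lost then varies around 21 and can by chance be 14 or fewer. Both models lead to the same conclusion.

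**The case against.** A reader might infer that the rule cannot be met whatever the app does. The article does not support that, for three reasons.

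- **Attrition is not defined as missing outcome data.** It could mean participants who stop answering calls. Their attendance can still come from the adult service or a hospital database, and the Participant timeline schedules a separate contact with the adult service at 6 months. The missing-data rule applies only to data that remain missing. If 7 of the 21 were confirmed attenders and all 49 others engaged, 49 + 7 = 56 and the rule is met. With 85% engagement among the 49, the chance of success is about 0.61 if each of the 21 has a 70% chance of being confirmed engaged, and about 0.16 if that chance is 50%.
- **The 30% has no time point.** Follow-up runs to 18 months and the primary outcome is at 6 months, so loss at 6 months may be lower.
- **The contact rule is ambiguous.** Its reference to 6 and 12 months can be read as requiring both contacts to fail.

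These points stand and make impossibility conditional. They do not rescue the power statement. Participants whose attendance is confirmed elsewhere are not lost to the primary analysis, so they give no reason to inflate 49 to 70. Read literally, the contact rule also fails people whom the Primary outcome section would allow to be confirmed as attenders.

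It is also fair to say that counting missing as failure is a cautious and defensible choice here, since being unreachable is plausibly related to not engaging. The difficulty is only that power was not computed under it.

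**Conclusion.** The concern holds as an internal inconsistency, not as an arithmetic error. The claim of at least 80% power describes 49 participants with complete data and an unstated true rate of about 85% or higher. It does not describe the planned analysis, which needs 56 of 70.

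Two results do not depend on the assumed 85%. If 21 of 70 are unascertained at 6 months, the rule cannot be met. The same is true for any number above 14. Whether this will happen is not settled by the article, because it neither dates the 30% nor says how many of those lost could be confirmed through other sources.

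Below that limit success is possible, but power falls quickly: under the 85% assumption with fixed loss, it is already 0.60 with 4 unascertained and 0.25 with 7.

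**What to change.** 1. **Restate the sample-size section.** Keep missing as failure for the primary analysis and remove the attrition inflation. Say that all 70 are analysed; that at least 56/70 must be confirmed engaged; that power is about 80% if 83% of all enrolled are confirmed engaged and 91% if 85% are; and that the rule is unattainable if more than 14 are unascertained at 6 months.
2. **Reconcile the contact rule with the Primary outcome section.** State that attendance confirmed by the adult service or a hospital database counts as engagement even when the young person cannot be reached.
3. **Add a sensitivity analysis** of participants with ascertained status, using the exact limit for the number actually ascertained. The 40/49 threshold applies only if that number is 49. Making this set the primary analysis is more debatable, because excluding unreachable participants would tend to raise the engagement rate.

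The cost is wording in the protocol and analysis plan. The stated power becomes less favourable, because the 83% refers to everyone enrolled. With 10% unascertained, for example, it implies about 0.83 / 0.90 = 92% engagement among the rest.

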### Recruitment

Participants will be recruited from the paediatric outpatient clinics within the Sydney Children’s Hospital Network (Sydney Children’s Hospital at Randwick and The Children’s Hospital at Westmead). Suitable patients aged 16 years and over with a chronic illness requiring transition to adult services in their final year of paediatric care/attending their penultimate paediatric appointment will be identified by the treating team or clinic staff and will be approached for recruitment to be part of the study by a member of the research team.

All clinical teams from the two tertiary children’s hospital across the network who may have potential study recruits will be contacted directly by the researchers. The researchers will present the TransitionMate study and application to the teams. Recruitment inclusion as well as exclusion criteria will be explained to the respective clinical teams. A contact person from each subspecialty will be identified to coordinate ongoing recruitment of patients who fit the recruitment inclusion criteria. The clinical team make the first approach and only when the patient has agreed to be approached by the researchers do the researchers contact them. The research team will discuss with the contact person from the respective clinical team as to the best avenue to approach the patients for recruitment. This may be in a different clinical setting including transition clinics, routine follow-up clinics and during planned admissions or clinical procedures. The research team will also coordinate with the hospital’s Trapeze transition services to identify potential recruits. The research team will provide ongoing updates and liaison with the contact person from each clinical team and transition services every 3 months. This will include prospective review of clinic lists to determine if there are patients who fulfil criteria for the study.

